## Methods

### Hypothesis and aims

We hypothesise that 9 hours of therapy with the NEIVATECH system, which combines dichoptic training with perceptual learning tasks and gamified elements in an immersive virtual reality (VR) environment, will provide greater improvements in visual function in children with anisometropic amblyopia than conventional patching.

To test our hypothesis, we intend to conduct a small-scale RCT in which 60 anisometropic amblyopic children aged 5-17 years with no history of treatment for amblyopia other than refractive correction alone will be randomly assigned to receive 18 half-hour active vision therapy sessions with the NEIVATECH system over a period of 3 months (group A) or 2 hours of daily patching at home for the same period of time (group B).

The primary outcome measure to be considered will be changes in distance BCVA before and after therapy. Secondary outcome measures will include near BCVA, CSF, binocular vision, stereopsis, fusional vergence, near convergence point and accommodative facility. Other valuable outcome measures to consider after the intervention will be satisfaction, adherence, acceptance and safety of the therapy. In addition, resting-state fMRI (rsfMRI) will also be performed on a subgroup of 5 patients from each group at the pre- and post-intervention visit to provide a rational explanation for the visual improvements obtained with the NEIVATECH system, if any.

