### Sampling

Consecutive sampling of all patients attending the pediatric ophthalmology units of the hospital centres planned for recruitment who met the eligibility criteria will be carried out over a period of 12 months (May 2022 to April 2022). The contact details of all patients who consent to participate will be registered in order that they can be contacted to arrange in-office active vision therapy sessions and scheduled visits. Participants will be assigned to the experimental or control group by block randomization using a computer-generated list of random numbers in order to ensure equal treatment allocation. Once randomized, each patient recruited in Valladolid will also be offered the possibility of participating in the rsfMRI study until the proposed number in each group is reached.

Sample size estimation for this study was carried out using the GRANMO online platform (https://www.imim.es/ofertadeserveis/software-public/granmo/), establishing a minimum distance BCVA difference to be detected in both groups before and after the intervention of 0.15 logMAR, a follow-up loss of 10% and a common standard deviation (SD) of 0.195 logMAR. According to this, a sample size of 30 patients per group would be required, considering an alpha error of 0.05 and a statistical power of 80%. This result is consistent with the sample size used in previous studies in this area [36–38].

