### Data analyses plan

A professional biostatistician has been consulted to design the data analysis plan for the study, in which descriptive analysis of all data will be provided, including means and SDs or medians for continuous variables and proportions for categorical variables.

Variables will be analyzed to assess distribution/normality (Kurtosis and Skewness) and by histogram analysis to establish whether they will be analyzed with parametric or non-parametric tests. On the one hand, parametric data will be analyzed using the unpaired T-test, Analysis of Variance (ANOVA) for comparison between groups and multiple linear regression to predict values according to the variables of interest. On the other hand, non-parametric data will be analyzed using the Mann-Whitney U test or the Chi-squared test, the Kruskal-Wallis H test and other non-parametric methods.

For the purposes of the rsfMRI study, analyses of grey matter, white matter diffusion and functional connectivity will be performed. To quantify the variation between the metrics obtained in the two acquisitions (pre-intervention and post-intervention), a coefficient of variation of (Mt_0_ − Mt_1_ / Mt_0_) × 100 will be used, where M will be the metric considered, t_0_ will correspond to the first acquisition (pre-intervention visit) and t_1_ will correspond to the second acquisition (post-intervention visit).

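### The primary outcome's test is left to the shape of the trial data, so the plan does not fix whether the arms are compared on mean BCVA or on ranks

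*Protocol article*

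**What the plan says.** The Data analyses plan section of the protocol article opens its rule with "Variables will be analyzed to assess distribution/normality (Kurtosis and Skewness", adds histograms, and says that these serve "by histogram analysis to establish whether they will be analyzed with parametric or non-parametric tests".

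Two branches follow:

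- Parametric: "parametric data will be analyzed using the unpaired T-test, Analysis of Variance (ANOVA) for comparison between groups", plus multiple linear regression for prediction.
- Non-parametric: "non-parametric data will be analyzed using the Mann-Whitney U test or the Chi-squared test, the Kruskal-Wallis H test and other non-parametric methods".

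The rule is written for variables in general. The primary outcome is defined under Hypothesis and aims: "The primary outcome measure to be considered will be changes in distance BCVA before and after therapy". No test is tied to it and it is not exempted, so the rule governs it. The article gives no threshold for skewness or kurtosis.

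The Sampling section sizes the trial by "establishing a minimum distance BCVA difference to be detected in both groups before and after the intervention of 0.15 logMAR", with "a follow-up loss of 10% and a common standard deviation (SD) of 0.195 logMAR", alpha 0.05 and 80% power, giving 30 per group.

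**The concern.** A confirmatory comparison should have its hypothesis fixed before the data are seen. Here the observed distribution decides between two tests that do not ask the same question. The t-test compares mean change in logMAR, while Mann-Whitney asks whether values in one arm tend to exceed those in the other. The two coincide when the arms differ only by a shift, and separate when the arms differ in shape. Shapes could differ if, for instance, one treatment helps some children a great deal and others not at all.

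Two things are at stake. The headline result may not be on the scale for which the trial was sized. And whoever judges the histograms has discretion over the primary test. The trial is open-label, and the blinding described under Study design is for the endpoint evaluators.

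**Working it through.** **Inputs.** From Sampling: difference 0.15 logMAR, SD 0.195, alpha 0.05, power 80%, loss 10%, equal allocation. Assumed: two-sided testing (not stated), the outcome shapes used below, and the cut-offs for the rule, since the article gives none.

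**1. Reproduce the sample size as a comparison of means.**

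n = 2 × (1.960 + 0.842)² × (0.195/0.15)² = 2 × 7.85 × 1.69 = 26.5, so 27 per group.

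With 10% loss: 27/0.90 = 30 per group. The stated figure is reproduced. A one-sided test would give 21, or 24 with loss, and does not match.

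**2. The same target under the rank branch.** With normal data the relative efficiency of Mann-Whitney is 3/π, so 27/(3/π) = 28.3, or 29 evaluable, and 29/0.90 = 32.2, or 33 per group. The stated 30 belongs to the mean branch.

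**3. Simulate the rule.** There were 27 per arm, SD 0.195 and 20,000 trials per scenario, with both arms of the same shape. Two assumed rules send the analysis to Mann-Whitney: (a) absolute skewness or excess kurtosis of the within-arm residuals above 1; (b) skewness or kurtosis test significant at 5%. Either test means rejecting when at least one of the two p-values is below 0.05. All entries are percentages.

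| Shape | Switch to MW, a / b | Type I: t | Type I: MW | Type I: rule a / b | Type I: either test | Power at 0.15: t | Power at 0.15: MW | Verdicts differ at 0.15 |
|---|---|---|---|---|---|---|---|---|
| Normal | 6 / 9 | 4.9 | 4.7 | 5.0 / 5.0 | 5.8 | 79.5 | 77.0 | 5.9 |
| t, 4 df | 57 / 55 | 4.8 | 4.9 | 5.3 / 5.3 | 6.2 | 80.5 | 88.8 | 10.1 |
| Lognormal (0.6) | 81 / 97 | 4.6 | 4.6 | 4.9 / 4.7 | 6.4 | 80.7 | 94.5 | 14.1 |
| Exponential | 88 / 99 | 5.0 | 4.9 | 5.2 / 4.9 | 6.8 | 79.6 | 94.4 | 15.2 |

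Separate runs with normal data and with moderately skewed data (gamma, shape 2) gave a type I error of 4.7-5.2% for a mechanical rule and about 5.4-6% for either test.

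**4. Direction of the disagreement.** In a gamma run of 8,000 trials with a true 0.15 difference, the verdicts differed in 10.8%. Mann-Whitney alone was significant in 10.0% and the t-test alone in 0.7%; power was 88.5% against 79.3%. A further run gave 11.2%, of which 10.2 points were Mann-Whitney alone.

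**5. Arms of different shape.** With equal means, one arm normal and the other exponential (a deliberately strong contrast), the t-test rejected in 5.2% of trials, Mann-Whitney in 7.6% and rule (a) in 7.3%. Equal means is the null hypothesis of the first test but not of the second, so the branch taken decides which hypothesis is tested.

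**The case against.** The case on the other side is substantial, and much of it stands.

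- **Validity.** A reader might infer that the p-value is invalid or type I error badly inflated. The text does not support that. It lets the distribution decide, not the smaller p-value, and a mechanical rule stays near nominal when the arms share a shape. Nor does anything say that both tests would be run and compared first.
- **Disagreement between tests.** A reader might count the roughly 11% of differing verdicts under skew as harm. Nearly all of them are true effects that the rank test finds and the t-test misses.
- **Estimate and adjustment.** A reader might infer that the rank branch can yield no logMAR estimate and no covariate adjustment. That goes too far. A Hodges-Lehmann shift is on the logMAR scale; in the gamma scenario it averaged 0.149 (SD 0.044), against 0.150 (SD 0.053) for the mean difference. The open-ended end of the non-parametric list does not exclude adjusted methods. The article simply names neither.
- **Article versus full plan.** Cut-offs and the pairing of tests with outcomes are details that an article may leave to a fuller plan. That is fair for the missing cut-off. It does not dispose of the point, because the article positively states the data-dependent rule. A fuller plan that follows it inherits the problem, and one that names a single primary test contradicts it.
- **Choice of model.** An unpaired t-test on change would also match the sample size. This is true: any single prespecified mean comparison closes the gap, and baseline adjustment is an improvement on top.

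**Conclusion.** The concern holds in a limited form. The plan fixes a data-driven choice of test that covers the primary outcome, so it does not settle whether the primary hypothesis concerns means or ranks, while its sample size belongs to means. The consequence is an unfixed estimand and analyst discretion.

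The numerical cost in type I error is small: 4.7-5.3% under the assumed mechanical rules with same-shaped arms. If either test may be taken, it is about 5.4-6% with normal or moderately skewed data, reaching 6.8% in the most skewed case tried. The 7.3% in the different-shapes case illustrates that the hypotheses differ; it does not predict this trial.

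These figures rest on assumed shapes and cut-offs and on 27 evaluable per arm. The change should be made, but the trial is not undermined without it.

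**What to change.** For the primary outcome, delete the distribution-based choice and prespecify one analysis:

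- a linear model of day-90 distance BCVA in the amblyopic eye on treatment, adjusted for baseline BCVA;
- the mean difference in logMAR with its 95% confidence interval as the reported result;
- robust or bootstrap standard errors, with one of the two named now and used unconditionally. Making them depend on skewed residuals would bring back the same kind of data-driven choice.

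With baseline in the model, the treatment coefficient is the same whether day-90 BCVA or its change from baseline is the outcome, so the analysis still addresses the stated primary outcome.

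Keep Mann-Whitney with a Hodges-Lehmann estimate as a labelled sensitivity analysis. Assign each secondary outcome its method by measurement scale (continuous, ordinal, binary), not by its observed histogram.

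The cost is wording only. Baseline BCVA is already measured, and 30 per group is unchanged. The downside is some efficiency lost to a rank test if the data prove strongly skewed; the unadjusted comparison above (79.3% against 88.5% power with gamma data) indicates the order of that loss.

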### Mid-intervention (day 30 and 60)

After 1 and 2 months of therapy, the patient will be referred for re-evaluation of the visual outcome measures.

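### The named between-arm tests on change in distance BCVA are valid at month 3 but leave out baseline BCVA as a covariate and the month 1 and 2 data, so precision is given away

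*Protocol article*

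**What the plan says.** Under Hypothesis and aims, the protocol article defines the endpoint: "The primary outcome measure to be considered will be changes in distance BCVA before and after therapy". Acuity is assessed at the pre-intervention visit, and the Mid-intervention section adds two further assessments: "After 1 and 2 months of therapy, the patient will be referred for re-evaluation of the visual outcome measures". Day 90 is the post-intervention visit, so each child contributes up to four values.

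For the group comparison, the Data analyses plan states that "parametric data will be analyzed using the unpaired T-test, Analysis of Variance (ANOVA) for comparison between groups". Mann-Whitney, chi-squared and Kruskal-Wallis tests are the non-parametric counterparts. Multiple linear regression is also listed, but for prediction; it is not tied to the treatment effect, and no covariates are given.

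The Sampling section sizes the trial by "establishing a minimum distance BCVA difference to be detected in both groups before and after the intervention of 0.15 logMAR", with "a follow-up loss of 10% and a common standard deviation (SD) of 0.195 logMAR", and concludes that "a sample size of 30 patients per group would be required". Allocation is by "block randomization using a computer-generated list of random numbers in order to ensure equal treatment allocation". Stratification by baseline acuity is not mentioned.

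**The concern.** Every test named for comparing the arms takes one number per child and compares two independent sets. Applied to the change score, this uses baseline only by subtraction, which amounts to fixing the regression slope of day-90 acuity on baseline at 1. When the two variances are equal and the correlation r is below 1, the best-fitting slope is r, so subtraction over-corrects. This has two consequences.

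- **Precision.** The change score carries more variance than an estimate that fits the slope from the data.
- **Chance imbalance.** If one arm starts with worse acuity by chance, a fraction (1−r) of that difference stays in the estimated treatment effect. Randomisation removes this on average over repeated trials, but not within a single trial of 60 children.

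The month 1 and 2 values also have no role in the day-90 comparison, although they carry information about children whose day-90 value is missing. The plan allows for 10% loss on top of a requirement of 27 per arm, so there is little slack.

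**Working it through.** **Inputs from the protocol article (Sampling).** Difference 0.15 logMAR; SD 0.195 logMAR; alpha 0.05; power 80%; loss 10%; equal allocation. Sidedness is not stated.

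**Inputs that are assumed.** The correlation r between baseline and day-90 BCVA is not given; I use 0.5 to 0.8. Variances at the two times are taken as equal. The article does not say whether 0.195 is the SD of change or of a single measurement; the main calculation takes it as the SD of change.

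**1. The plan's own figure.**
n per arm = 2 × [0.195 × (1.960 + 0.842) / 0.15]² = 26.5, rounded up to 27. Allowing for loss: 27 / 0.90 = 30. The stated 30 per group is reproduced with a two-sided test. A one-sided test gives 21, or 24 after loss, and does not match. An unpaired comparison of change is therefore consistent with the sample size. Its power with 27 evaluable per arm is 79.2% by the noncentral t distribution (80.7% by the normal approximation).

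**2. Variance ratio.** With single-visit SD s:
- variance of change: 2s²(1−r)
- residual variance after adjusting for baseline: s²(1−r²)
- ratio: (1−r²) / [2(1−r)] = (1+r)/2

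**3. Power with 27 per arm at 0.15 logMAR, 0.195 as SD of change.** The effective SD is 0.195 × √[(1+r)/2].

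| r (assumed) | Variance ratio | Effective SD | Power (t) | Power (normal) |
|---|---|---|---|---|
| change score | 1.00 | 0.195 | 79% | 81% |
| 0.5 | 0.75 | 0.169 | 89% | 90% |
| 0.6 | 0.80 | 0.174 | 87% | 89% |
| 0.7 | 0.85 | 0.180 | 85% | 87% |
| 0.8 | 0.90 | 0.185 | 83% | 85% |

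The degree of freedom spent on the covariate changes power by less than 0.1 percentage point. Put as sample size, the 27 evaluable per arm would fall to 20, 23 and 24 at r = 0.5, 0.7 and 0.8.

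**4. Chance imbalance left in a change score.** The residue is (1−r) times the baseline difference.
- If 0.195 is a single-visit SD, the standard error of the baseline difference is 0.195 × √(2/27) = 0.053 logMAR. An imbalance of two standard errors leaves 0.5 × 0.106 = 0.053 at r = 0.5, or 0.2 × 0.106 = 0.021 at r = 0.8.
- If 0.195 is the SD of change, the single-visit SD is 0.195 / √[2(1−r)], which is 0.195 at r = 0.5 and 0.308 at r = 0.8. The same two-standard-error imbalance leaves 0.053 and 0.034.

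So an imbalance of this size, which would be unusual, moves the estimate by roughly 0.02 to 0.05 logMAR against a target of 0.15.

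**5. Intermediate visits.** No figure is computed for the gain from months 1 and 2. It arises mainly where the day-90 value is missing and depends on between-visit correlations that the article does not give.

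**The case against.** The strongest reply is that nothing here is an error. The two arms hold different children, so an unpaired test of change is a standard and valid analysis. It keeps its 5% error rate, is unbiased under randomisation, and is the test for which the trial was sized. All of that stands.

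It can also be said that covariates and models commonly sit in a full analysis plan, which is not shown, and that the listed multiple regression could carry arm and baseline. That stands in part. Regression could do this work, but the article assigns it to prediction and assigns the group comparison to the unadjusted tests. The point is therefore about a choice the article makes, not about detail it omits.

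The size of the gain is assumed, and at r = 0.8 it is only about four points of power. That also stands.

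Three stronger readings are tempting, and the document supports none of them:

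- **That baseline acuity is ignored.** The outcome is a change, so baseline is used by subtraction. What is missing is its use as a covariate.
- **That visits will be pooled as independent observations, inflating type I error.** With two arms, ANOVA and Kruskal-Wallis add nothing to the t-test and Mann-Whitney, so a reader might infer that they are meant for comparing visits. The text gives ANOVA for comparing groups, the outcome is a before-and-after change, and pooling is stated nowhere.
- **That children lost before day 90 will be excluded.** The article states no such rule.

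**Conclusion.** The point holds as a loss of efficiency, not as an invalid analysis. For one month-3 contrast the named tests are sound and match the stated 30 per group. Adjusting for baseline BCVA would reduce variance by 25% to 10% and raise power from about 79% to between 89% and 83% at 27 per arm. It would also remove the (1−r) share of any chance baseline imbalance.

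These figures rest on three assumptions: r between 0.5 and 0.8, equal variances at baseline and day 90, and 0.195 being the SD of change. The direction does not depend on the exact r: with equal variances the ratio is below 1 for every r below 1. No inflation of the error rate is shown. The change is worth making because it costs almost nothing and the design has little spare power.

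**What to change.** Name one primary contrast: the difference between arms in amblyopic-eye distance BCVA at day 90, with a 95% CI. Estimate it by ANCOVA with baseline BCVA as covariate. Alternatively, fit a mixed model to days 30, 60 and 90 with arm, visit, arm-by-visit and baseline BCVA, allowing for correlation within child, and keep the day-90 contrast as primary. Keep the unadjusted t-test on change as a sensitivity analysis. State whether 0.195 is the SD of change or of a single measurement.

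The cost is a change of analysis wording and a few lines of code. All the measurements are already scheduled and the sample size need not change. The change should be fixed before outcome data are seen.

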### Study design

This is a multicentre, open-label, small-scale RCT involving two tertiary hospital centres with an on-site pediatric ophthalmology unit in their facilities. The protocol for this study was designed according to the SPIRIT (Standard Protocol Elements: Recommendations for Interventional Trials) 2013 Statement (Supplementary file 1). Patients will be offered to participate in the study once they have been found to meet all inclusion criteria without fulfilling any exclusion criteria (Table 1).

**Table 1 Tab1:** Eligibility criteria for participation in the NEIVATECH RCT

Inclusion criteria	
- Children aged between 5 and 17 years. - Willingness to perform the assigned therapy and to carry out the established visits. - No history of previous treatment for amblyopia other than optimal refractive correction for at least 2 months prior to inclusion in the study. - BCVA in the amblyopic eye of ≤0.1 logMAR with at least 1 logMAR line difference between the two eyes of the same patient. - Presence of anisometropia defined as a difference in spherical equivalent between the two eyes of ≥1.5 dioptres.	
Exclusion criteria	
- Active eye disease. - Previous ocular surgery. - BCVA in the amblyopic eye of ≥0.70 logMAR. - Presence of strabismic or deprivation amblyopia. - Presence of microtropia or intermittent strabismus. - Presence of irregular cornea due to astigmatism or ectatic corneal disease. - Presence of psychiatric or neurological disorders or cognitive impairment.	

Prior to participation, trained research staff will obtain written informed consent from the patient or the patient’s parents or legal guardians depending on whether the patient is older or younger than 16 years of age. For the rsfMRI study, patients will have to meet specific eligibility criteria and sign a separate informed consent form to undergo testing (Table 2).

**Table 2 Tab2:** Eligibility criteria for participation in the rsfMRI study

Inclusion criteria	
- Inclusion in the NEIVATECH RCT. - Written informed consent for rsfMRI.	
Exclusion criteria	
- Claustrophobia. - Pregnancy or breastfeeding. - Presence of a pacemaker or other cardiac device. - Presence of an external or implantable insulin pump. - Presence of metallic implants or intracorporeal foreign bodies.	

Patients may leave the study once they have completed all visits as outlined in the protocol or whenever they wish by contacting the principal investigator and signing a waiver form.

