To minimize the risk of bias, this study will be blinded to the endpoint evaluators through the adoption of a PROBE (Prospective Randomized Open, Blinded End-point) design.

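### The single rsfMRI change formula needs its bracket and name corrected and does not suit signed connectivity metrics; separately, scan consent is sought after open allocation

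*Protocol article*

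**What the plan says.** The Data analyses plan names three families of imaging analysis ("analyses of grey matter, white matter diffusion and functional connectivity will be performed") and then gives one measure of pre-to-post change. Its purpose is stated as "To quantify the variation between the metrics obtained in the two acquisitions", and its form is "a coefficient of variation of (Mt_0_ − Mt_1_ / Mt_0_) × 100 will be used". M stands for whichever metric is being considered, t0 for the scan before the intervention and t1 for the scan after it. No separate rule is given for connectivity, and the connectivity metric is not defined.

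The sub-study has five children from each group (Study overview). They enter as follows: "Once randomized, each patient recruited in Valladolid will also be offered the possibility of participating in the rsfMRI study". Offers stop when both quotas of five are full (Sampling). Scanning needs its own eligibility check and its own signed consent (Study design). The same section says "This is a multicentre, open-label, small-scale RCT". Blinding is confined to outcome assessment: "this study will be blinded to the endpoint evaluators".

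The scans have three uses: to examine what each therapy does to plasticity in the visual cortex (Abstract), to help explain any visual gains with the VR system (Hypothesis and aims), and, as an attempt, to be correlated with those gains (Discussion).

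**The concern.** There are two distinct issues, with different causes and different fixes.

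The first is the change measure. As shown, only the second value is divided by the first, so the expression is not a relative change. Its label belongs to another quantity, the standard deviation divided by the mean. Restoring the bracket settles this for metrics that are always positive and well away from zero. It does not settle it for a metric that can be zero or negative, because the baseline in the denominator then controls both the size and the sign of the result. In a group of five, one such child can decide the group mean.

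The second is how the ten children come to be scanned. If a family can know its arm when it accepts or declines, those who accept in one arm may differ from those who accept in the other. Randomisation does not protect a comparison formed in that way.

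**Working it through.** **Inputs.** From the protocol article: the formula and the metrics it covers (Data analyses plan), five children per group (Study overview), the timing of the offer (Sampling), and the open-label design with separate scan consent (Study design). The article gives no rsfMRI values, so every value of M below is an assumption chosen for illustration. There is no stated rsfMRI result to reproduce.

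**Step 1: what the formula is meant to be.** Read literally, the expression is (M0 − M1/M0) × 100. When nothing changes (M1 = M0) this equals (M0 − 1) × 100, which is zero only if M0 happens to be 1. A measure of change should be zero whenever nothing changes. The stated purpose, the outer bracket and the factor of 100 all point to

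D = ((M0 − M1)/M0) × 100.

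This is zero under no change and does not depend on the unit. For a positive metric, D is negative when the metric rises and positive when it falls. The remaining steps use D.

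**Step 2: the same rise from different baselines.** Each row is a rise of 0.10. The last column is the difference on the Fisher-z scale, z = 0.5 × ln((1 + r)/(1 − r)), for the case where M is a correlation.

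| M0 | M1 | D | M1 − M0 | z1 − z0 |
|---|---|---|---|---|
| 0.50 | 0.60 | (−0.10/0.50) × 100 = −20% | +0.10 | 0.693 − 0.549 = +0.144 |
| 0.05 | 0.15 | (−0.10/0.05) × 100 = −200% | +0.10 | 0.151 − 0.050 = +0.101 |
| −0.05 | 0.05 | (−0.10/−0.05) × 100 = +200% | +0.10 | 0.050 − (−0.050) = +0.100 |

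A fall from 0.05 to −0.05 also gives (0.10/0.05) × 100 = +200%, the same as the rise in the last row. D therefore cannot tell the two apart. At M0 = 0 it is undefined. The plain and Fisher-z differences keep one sign throughout and are defined at zero.

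**Step 3: a group of five.** Assume baselines of 0.50, 0.40, 0.30, 0.20 and −0.05, each rising by 0.10. D is −20, −25, −33.3, −50 and +200.

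- Mean: (−20 − 25 − 33.3 − 50 + 200)/5 = 71.7/5 = +14.3%. Under this formula that reads as a fall, although all five values rose.
- Median: −25%, which has the right direction.

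**Step 4: dependence on the baseline.** Assume normally distributed baselines with SD 0.15, a true mean rise of 0.10 and an SD of change of 0.05. In simulation, the share of true rises that D signs wrongly, and the central 95% range of D, were:

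- baseline mean 0.6: about 0%, range about −44% to 0%;
- baseline mean 0.3: 2.3%, range about −210% to +16%;
- baseline mean 0.1: 25%, range about −874% to +831%.

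The problem is negligible for values well above zero and serious for values near it.

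**Step 5: selection into the sub-study.** No arithmetic applies. Set side by side, the Sampling section places the offer after randomisation, and the Study design section makes the trial open-label, blinds only the evaluators and requires a separate consent. Nothing in the article keeps the arm from the family until the scan decision is made. Offering the scan to each Valladolid child until the quotas fill limits choice by staff, but it does not limit choice by families.

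**The case against.** **The bracket.** A stacked fraction flattened to one line looks exactly like the text shown, and the intended meaning is clear. A reader might infer that the literal expression will be run and give meaningless numbers. The documents do not support that. This part of the point is a correction of notation and label.

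**The sign.** Subtracting the later value from the earlier one is unusual, but t0 and t1 are defined, so it is a convention and not an error. It only needs to be stated so that a rise is not read as a fall.

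**Connectivity.** The article never names the metric. A reader might infer that the formula must fail for connectivity, but a strictly positive summary would not fail in this way, and the full protocol may define one. The objection stands to that extent, and the criticism is conditional. What remains is that the article fixes one formula for all metrics with no such restriction.

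**Robust methods.** The plan allows medians and non-parametric tests after a check of distributions. These limit the pull of one extreme value, as the median in Step 3 shows. They do not repair values whose sign is already wrong, and they cannot handle a zero baseline.

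**Size of the sub-study.** A reader might infer that five per group is itself an error. The article makes no power or sample-size claim for rsfMRI, so the small number is not evidence of one.

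**Use of the formula.** The Discussion speaks of an attempt to correlate imaging findings with visual gains. It does not say that this percentage is the quantity to be correlated.

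**Selection.** Nothing shows that uptake will differ by arm. A reader might infer that the contrast is biased. The documents support only a risk.

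**Conclusion.** The point holds in a limited form. The expression lacks its inner bracket and is misnamed, and both are certain from the text as shown. With the bracket restored, it is sound for strictly positive metrics well away from zero. For a signed or near-zero connectivity metric it is not. On assumed values, an identical rise of 0.10 runs from −200% to +200% depending on the baseline, and one negative baseline among five turns a uniform rise into a mean of +14.3%, which reads as a fall. This conclusion depends on what the connectivity metric is, and the article does not say.

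On selection, the order of events in the plan leaves the five-against-five contrast without the protection of randomisation. The direction and size of any resulting bias are unknown.

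Both issues concern an exploratory sub-study of ten children. The primary BCVA comparison is unaffected.

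**What to change.** 1. Write the formula with its bracket, ((M0 − M1)/M0) × 100, call it percentage change, and state that a positive value means a decrease. Alternatively, reverse the subtraction and say so.
2. Restrict it to strictly positive metrics. For connectivity metrics that can be zero or negative, use the plain difference M1 − M0, on the Fisher-z scale if the metric is a correlation.
3. In Valladolid, seek rsfMRI consent before allocation is revealed, and scan the first five consenters in each arm.

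The first two changes cost only wording. The third moves one consent step earlier, and its price is that more families are asked than are scanned. If recruitment has already begun under the present order, report how many families in each arm were offered the scan and how many declined, and describe the two imaging groups as not protected by randomisation.
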